#### 8.1.2 Secondary study parameters/endpoints

Different secondary parameters will be measured to determine the influence of the PARASOL intervention on general health, physical behaviour, perceptions, self-efficacy and cost-effectiveness.

- Severity of symptoms, defined as self-perceived pain and fatigue in the past week, will be measured with an 11-point numeric scale (score 0-10)(50).

- Severity of psychosocial symptoms will be measured with 4DKL questionnaire.

This questionnaire consists of four subscales (distress, depression, anxiety, somatisation)(51,52).

- Health care use and indirect costs through illness and absenteeism will be measured with TIC-P questionnaire to evaluate cost-effectiveness for social perspective in terms of costs per 'Quality Adjusted Life Years (QALYs)(53)'. QALYs will be measured using the SF-6D scores (according to SF-36 questionnaire)(53,54), which is a valid and reliable method(53).

- Physical behaviour will be measured with the Activ8 activity monitor(55). The Activ8 is a valid measurement in detecting lying, sitting, standing, walking, running and cycling. In this way, physical behaviour can be measured accurate. Subjects will wear the Activ8 activity monitor for one week. They can wear the Activ8 activity

monitor in their pants pocket without recharging it during the week. There are accessories as straps available in case subjects does not have pockets.

- Illness perceptions will be measured with the Brief Illness Perception Questionnaire. This questionnaire is an eight-item scale designed to assess cognitive and emotional representations of illness on an ordinal scale (0-10)(56,57).
- Self perceived health will be measured with the EQ5D questionnaire. This questionnaire will measure the perceived health on five levels (i.e. mobility, self-care, usual activities, pain/discomfort and anxiety/depression)(58).
- Self-efficacy will be measured with the Hei-Q questionnaire, which is a user friendly, valid and reliable questionnaire specifically developed in evaluating patients education and self-management programmes in patients with chronic complaints(59).

Besides the above parameters, efficacy, barriers and facilitators of the PARASOL intervention according to participating subjects and professionals will also be determined, using the 'System Usability Scale (SUS)'. The SUS will be completed at T1, at the end of the PARASOL intervention. The questionnaire will measure the perceived usability by ten statements which can be scored on a 5-point Likert scale ('totally agree' to 'totally disagree'). The SUS is a simple, valid and reliable measurement and is often used to evaluate the usability of eHealth applications(60).

### **8.1.3 Other study parameters**

Demographic and clinical baseline variables such as age, gender, education level, work situation, duration of complaints and possible co-morbidities will be measured at baseline. Demographic and clinical variables will only be completed at baseline.

## **8.2 Randomisation, blinding and treatment allocation**

We will recruit health care centers that fulfil the inclusion criterion. Co-applicants Leidsche Rijn Julius Gezondheidscentra (5 health care centers, 40.000 patients) and Stichting Gezondheidscentra Eindhoven (10 health care centers, 80.000 patients) are already willing to participate (co-applicants of the NWO grant proposal). The participating health care centers will be randomized to either the experimental group or the control group. Through cluster randomization, we will avoid the possibility of professionals offering both experimental and control intervention. In this way we also avoid that professionals who offer the experimental or control intervention within one health care center will influence each other (contamination-effect)(61). After randomization, the selection and inclusion procedure of subjects with moderate MUPS will be performed. In the health centers in the experimental group, patients with moderate MUPS will be offered the PARASOL intervention. In the control group health centers, patients with moderate MUPS will get care as usual.

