### 4.3 Exclusion criteria

Eligible subjects will be excluded when the subject has:

- insufficient mastering of the Dutch language
- no access to the internet.

Furthermore, all identified subjects with moderate MUPS using the PRESUME screening method will be screened by their GP. The GP will exclude the subjects if one or more of the following criteria apply:

- received a medical explained diagnosis between identification using the PRESUME method and the time of inclusion.
- complaints with a shorter duration than one month, in which more diagnostic evaluation of the symptoms is needed.
- unable to participate according to the GP, f.i. because of a life threatening condition, a shortened life expectancy, a major life event in the past month or a MUPS targeted multidisciplinary intervention in the past 12 months.
- the diagnostic phase has not been completed, in other words there is no agreement between GP and patient about sufficient diagnostic testing to rule out a physical cause

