## **8.3 Study procedures**

### Recruitment of subjects

After randomization of the health care centers, the health care centers will perform the PRESUME screening method using the electronic medical record of the GPs to identify subjects with moderate MUPS. The identified subjects will proactively be approached by the GP by sending them a letter as well as an information letter about the PARASOL study. The GP will send a reminder to the subjects who did not respond two weeks after sending the information letter. Another two weeks later, an assistant of the health care centers will contact the subjects by phone to see if they are willing to participate. When a subject is willing to participate, he can contact the researcher by phone or by mail. The researcher will answer possible questions, give further information, and will ask if the subject is willing to participate. When a subject is willing to participate, an appointment for signing informed consent will be made. After signing informed consent, baseline measurements will be completed (see patient report form) (see Chapter 8.1). After the baseline measurements, subjects of the experimental health care centers will be contacted by phone to make an appointment for the intake with the physical therapist and mental health nurse. Subjects of the control health care centers will be contacted three, six, nine and twelve months after completing baseline measurements for the follow-up measurements. In the meantime, they can receive care as usual (see figure 1). Subjects of the control health care centers will be offered the PARASOL intervention after the last follow-up measurement, twelve months after completing the baseline measurements. When their insurance does not cover the physical therapy part, the PARASOL intervention will be offered for free.

The total duration of the PARASOL study for all subjects (both experimental group and control group) will be twelve months. The PARASOL intervention for the subjects of the experimental group will start after the baseline measurements with an intake at the physical therapist and the mental health nurse and has a duration of twelve weeks.

Besides the above recruitment of subjects we will add two other recruitment strategies to increase the number of subjects. The first strategy is that GPs can recruit patients who are visiting the GP for consultation. The GP can recruit patients according to the following criteria:

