- patients  $\geq 18$  years with  $\geq 5$  general practice consultations during the past twelve months
- GP cannot medically explain the symptoms
- GP already completed the diagnostic phase in accordance with the patient

When a patient is eligible, the GP can give the patient the information letter about the PARASOL study. In addition, the GP will ask if the researchers can contact the patient by phone. If the patient agrees, the GP will inform the researchers and give the name and phone number of the patient.

A second strategy will be an open recruitment in the participating health care centers. Flyers with information of the PARASOL study will be laid down in the waiting rooms. In addition, the flyer will be added in the newsletter of Leidsche Rijn Julius Gezondheidscentra as well as the newsletter of Stichting Gezondheidscentra

Eindhoven and will be send to all patients by mail. Patients who are willing to participate can contact the researcher by phone or by mail. Subsequently, the researcher will contact the GP to check eligibility of the patient according to the above criteria.

Besides the two new recruitment strategies, the GPs in the participating health care centers mentioned that patients had difficulties in understanding the information letter. Therefore, we would like to add the flyer besides sending the letter of the GP and the information letter about the PARASOL study for the remaining 520 patients identified by the PRESUME screening method and selected by the GP.

The researcher will contact the subject by phone to make an appointment for the baseline assessment which will be performed by subjects at home. At the baseline assessment patient report form A will be completed, subjects will be informed and instructed about wearing the Activ8 activity monitor and patient report form B.

Subjects will be asked to carry the Activ8 for one week to measure their physical behaviour as well as requested to complete patient report form B digitally. After one week, they can send the Activ8 back by mail. Subjects are asked to complete the adequate relief question weekly between T0 and T1.

The first follow-up measurement (T1) will be three months after baseline. Subjects will be asked to complete the follow-up measurements and to carry the Activ8 for one week.

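### Patients are identified, screened by their GP and recruited after their centre has been allocated, with no concealment described, so the arms are only partly protected from selective recruitment

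*Protocol*

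**What the plan says.** - **Order.** Section 8.2 places selection after allocation: "After randomization, the selection and inclusion procedure of subjects with moderate MUPS will be performed". Section 8.3 says the same of identification: "After randomization of the health care centers, the health care centers will perform the PRESUME screening method". Section 11.2 repeats it.
- **Screening by the GP.** Section 4.3 states that "all identified subjects with moderate MUPS using the PRESUME screening method will be screened by their GP". One ground for exclusion is "unable to participate according to the GP", followed by examples rather than a closed list.
- **Approach.** Section 8.3: "The identified subjects will proactively be approached by the GP by sending them a letter". The GP also sends the reminder, and a centre assistant telephones those who have not answered. The researcher then handles questions and consent, and baseline follows consent.
- **Added routes.** Sections 8.3 and 11.2 add that "GPs can recruit patients who are visiting the GP for consultation", and open recruitment by flyer and newsletter with eligibility checked through the GP. The criteria for both are age, a count of consultations, a completed diagnostic phase and "GP cannot medically explain the symptoms". They do not include the section 4.2 condition of three consultations under listed ICPC codes.
- **Concealment.** Section 8.2 has blinding in its title but says nothing about blinding, or about hiding the arm from GPs, centre staff, the researcher or patients.

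**The concern.** Randomising centres makes the centres comparable in expectation. It makes the recruited patients comparable only if recruitment within centres does not depend on the arm. Here every step between the patient list and consent follows allocation, and several steps leave room for judgement or preference. An experimental centre can offer an active programme now. A control centre offers usual care and PARASOL after twelve months, and section 11.4 acknowledges that control patients gain nothing from taking part during the study. Patients who join could therefore differ between arms in motivation, expectation or severity before treatment starts.

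Both primary outcomes, adequate relief and RAND-36, are self-reported, so such differences could feed into the treatment comparison. Intention-to-treat analysis keeps the groups as recruited; it does not correct how they were recruited.

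**Working it through.** The point rests on who acts when, so the sections come first and the arithmetic is illustrative.

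**1. Does the GP know the arm?** No sentence states it. Section 4.2 makes the GP one of the disciplines that a participating centre must have, section 8.2 offers PARASOL only in experimental centres, and no concealment is described. Knowledge of the arm is a strong inference.

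**2. Which steps can depend on the arm?**

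| Step | Basis of decision | Room for selection |
|---|---|---|
| PRESUME query (4.2) | Fixed thresholds in the record | Little |
| GP exclusion (4.3) | Listed grounds plus GP discretion | Some |
| Recruitment in consultation (8.3) | GP judgement, no ICPC filter | More |
| Flyer and newsletter (8.3) | Self-referral, then GP check, no ICPC filter | More |
| Consent (4.4, 8.3) | Patient's choice, 40% response expected | Much |

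On consent, section 4.4 expects 54 × 0.40 = 21.6 participants per practice, so about 32 of 54 identified patients would not join.

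**3. What could an imbalance do?** Inputs from section 4.4: SD 23.8, ICC 0.04, 20 patients per centre, 206 patients (103 per arm). I take 206 as stated; whether it is the right number is a separate question.

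- Design effect = 1 + (20 − 1) × 0.04 = 1.76.
- Effective number per arm = 103 / 1.76 = 58.5.
- SE of the difference = 23.8 × √(2 / 58.5) = 4.40 points.
- With no true effect and a shift b from recruitment, the rejection probability of the two-sided 5% test is 1 − Φ(1.96 − b/SE) + Φ(−1.96 − b/SE).

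The shifts are assumptions; the protocol gives none.

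| Assumed shift | Points | b/SE | Type I error, unadjusted |
|---|---|---|---|
| 0.1 SD | 2.38 | 0.54 | 8.4% |
| 0.2 SD | 4.76 | 1.08 | 19.1% |
| 0.3 SD | 7.14 | 1.62 | 36.8% |

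Moving the SE between 4.30 and 4.43 gives 8–9%, 19–20% and 36–38%.

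**4. What if the shift is also present at baseline?** With adjustment for the baseline score and a baseline–follow-up correlation ρ, the remaining bias is b(1 − ρ) and the SE becomes 4.40 × √(1 − ρ²). For b = 4.76:

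- ρ = 0.5 (assumed): bias 2.38, SE 3.81, type I error 9.6%.
- ρ = 0.7 (assumed): bias 1.43, SE 3.14, type I error 7.4%.

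Adjustment therefore brings 19% down to about 7–10% if baseline shows the whole shift. It does not help where the groups differ in something that baseline does not measure.

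**The case against.** The strongest defence is that both arms share a good deal: an electronic query with fixed thresholds, one exclusion list, one sequence of letter, reminder and call for identified patients, consent through the researcher, and baseline before intake. The open exclusion ground comes with concrete examples, and the consultation route has written criteria. Control patients are promised PARASOL later, which narrows the difference in incentive. RAND-36, pain, fatigue, 4DKL and illness perceptions are measured at baseline, section 10.1 adjusts for confounders, section 10.3 compares the groups, and section 12.2 monitors inclusion rates and eligibility.

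Much of this stands, and it rules out three stronger readings:

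- A reader might infer that nothing makes the groups alike. The shared query and criteria contradict that.
- A reader might infer that any imbalance would be indistinguishable from a treatment effect. Measured differences can be seen and at least partly adjusted.
- A reader might take it as documented that GPs know the arm. It is an inference.

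What the defence does not cover is the remainder. The query governs only the first step of one route. The confounders are not named. Monitoring is not described by arm. No baseline test or covariate reaches unmeasured motivation or expectation. Adequate-relief responder status is counted from answers after T0, so it has no baseline value of its own to adjust for.

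**Conclusion.** The concern holds as a gap in protection. The protocol itself fixes the order of events and the recruiters, so this is not detail left to an analysis plan. GP discretion, the two added routes and consent leave room for unmeasured differences between arms, and the safeguards present are partial.

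A reader might go further and conclude that recruitment was biased, or that the type I error is 19% or 37%. The protocol gives no recruitment figures by arm, so neither the size nor the direction of any bias is known. Those percentages assume shifts of 0.2 and 0.3 SD with no adjustment; where baseline captures the shift, the 0.2 SD case falls to about 7–10% under the assumed correlations. The change should be made, but the trial is not invalid on this ground.

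**What to change.** **Centres not yet allocated, if any.** Run the PRESUME query on a fixed date and have the GP complete and lock the exclusion list, with a reason for each patient, before the arm is disclosed. Section 8.3 mentions 520 remaining patients already identified and selected by the GP, so for these at least the reversal comes too late.

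**Centres already allocated.**

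- Limit GP exclusions to the listed grounds and log a reason for each.
- Tabulate identified, excluded, invited and consented patients by arm, centre and recruitment route.
- Name the baseline outcome score as a covariate in the RAND-36 analysis.
- Pre-specify a sensitivity analysis restricted to PRESUME-identified patients, and state its limit: it addresses only the two added routes, because these patients also passed through GP exclusion and consent after allocation.

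**Cost.** A short delay before allocation is released where that is still possible, some logging at the centres, and one extra analysis that is less precise because it uses fewer patients.

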## **8.3 Study procedures**

### Recruitment of subjects

After randomization of the health care centers, the health care centers will perform the PRESUME screening method using the electronic medical record of the GPs to identify subjects with moderate MUPS. The identified subjects will proactively be approached by the GP by sending them a letter as well as an information letter about the PARASOL study. The GP will send a reminder to the subjects who did not respond two weeks after sending the information letter. Another two weeks later, an assistant of the health care centers will contact the subjects by phone to see if they are willing to participate. When a subject is willing to participate, he can contact the researcher by phone or by mail. The researcher will answer possible questions, give further information, and will ask if the subject is willing to participate. When a subject is willing to participate, an appointment for signing informed consent will be made. After signing informed consent, baseline measurements will be completed (see patient report form) (see Chapter 8.1). After the baseline measurements, subjects of the experimental health care centers will be contacted by phone to make an appointment for the intake with the physical therapist and mental health nurse. Subjects of the control health care centers will be contacted three, six, nine and twelve months after completing baseline measurements for the follow-up measurements. In the meantime, they can receive care as usual (see figure 1). Subjects of the control health care centers will be offered the PARASOL intervention after the last follow-up measurement, twelve months after completing the baseline measurements. When their insurance does not cover the physical therapy part, the PARASOL intervention will be offered for free.

The total duration of the PARASOL study for all subjects (both experimental group and control group) will be twelve months. The PARASOL intervention for the subjects of the experimental group will start after the baseline measurements with an intake at the physical therapist and the mental health nurse and has a duration of twelve weeks.

Besides the above recruitment of subjects we will add two other recruitment strategies to increase the number of subjects. The first strategy is that GPs can recruit patients who are visiting the GP for consultation. The GP can recruit patients according to the following criteria:

- patients  $\geq 18$  years with  $\geq 5$  general practice consultations during the past twelve months
- GP cannot medically explain the symptoms
- GP already completed the diagnostic phase in accordance with the patient

When a patient is eligible, the GP can give the patient the information letter about the PARASOL study. In addition, the GP will ask if the researchers can contact the patient by phone. If the patient agrees, the GP will inform the researchers and give the name and phone number of the patient.

A second strategy will be an open recruitment in the participating health care centers. Flyers with information of the PARASOL study will be laid down in the waiting rooms. In addition, the flyer will be added in the newsletter of Leidsche Rijn Julius Gezondheidscentra as well as the newsletter of Stichting Gezondheidscentra

Eindhoven and will be send to all patients by mail. Patients who are willing to participate can contact the researcher by phone or by mail. Subsequently, the researcher will contact the GP to check eligibility of the patient according to the above criteria.

Besides the two new recruitment strategies, the GPs in the participating health care centers mentioned that patients had difficulties in understanding the information letter. Therefore, we would like to add the flyer besides sending the letter of the GP and the information letter about the PARASOL study for the remaining 520 patients identified by the PRESUME screening method and selected by the GP.

The researcher will contact the subject by phone to make an appointment for the baseline assessment which will be performed by subjects at home. At the baseline assessment patient report form A will be completed, subjects will be informed and instructed about wearing the Activ8 activity monitor and patient report form B.

Subjects will be asked to carry the Activ8 for one week to measure their physical behaviour as well as requested to complete patient report form B digitally. After one week, they can send the Activ8 back by mail. Subjects are asked to complete the adequate relief question weekly between T0 and T1.

The first follow-up measurement (T1) will be three months after baseline. Subjects will be asked to complete the follow-up measurements and to carry the Activ8 for one week.

Six months and nine months after baseline, subjects will be asked to complete the cost-effectiveness questionnaire, since this questionnaire focuses on health related costs and indirect costs of the past three months. Additionally, subjects are asked to complete the adequate relief question monthly six months after baseline until T2.

The last follow-up measurement (T2) will be twelve months after baseline. Subjects will be asked to complete the follow-up measurements and to carry the Activ8 for one week. Table 1 gives a summary of all measures that will be collected with the different collection points.

Table 1: Summary of measures to be collected

| Primary outcome measures          | Data collection instrument                 | Follow-up measurements                              |       |                                                      |       |        |
|-----------------------------------|--------------------------------------------|-----------------------------------------------------|-------|------------------------------------------------------|-------|--------|
|                                   |                                            | Baseline                                            | 3 mo. | 6 mo.                                                | 9 mo. | 12 mo. |
| Impact of symptoms                | Adequate Relief question                   | X                                                   | X     |                                                      |       | X      |
|                                   |                                            | Weekly between baseline and 3 months after baseline |       | Monthly between six and twelve months after baseline |       |        |
| Quality of life                   | 36-Item Short Form Health Survey (RAND-36) | X                                                   | X     |                                                      |       | X      |
| Secondary outcome measures |                                            |                                                     |       |                                                      |       |        |
| Pain                              | Numeric Rating Scale (NRS)                 | X                                                   | X     |                                                      |       | X      |

|                                                       |                                                                                     |   |   |   |   |   |
|-------------------------------------------------------|-------------------------------------------------------------------------------------|---|---|---|---|---|
| Fatigue                                               | Numeric Rating Scale (NRS)                                                          | X | X |   |   | X |
| Severity of psychosocial symptoms                     | Four-Dimensional Symptom Questionnaire (4DKL)                                       | X | X |   |   | X |
| General health                                        | EuroQol - 5 Dimensions (EQ5D)                                                       | X | X |   |   | X |
| Physical behaviour                                    | Activ8 activity monitor                                                             | X | X |   |   | X |
| Illness perceptions                                   | Brief Illness Perception Questionnaire (IPQ-K)                                      | X | X |   |   | X |
| Self-efficacy                                         | Health Education Impact Questionnaire (Hei-Q)                                       | X | X |   |   | X |
| Cost-effectiveness                                    | Trimbos and iMTA questionnaire on Costs associated with Psychiatric illness (TIC-P) | X | X | X | X | X |
| Barriers and facilitators of the PARASOL intervention | System Usability Scale (SUS)                                                        |   | X |   |   |   |
| Other measures                                 |                                                                                     |   |   |   |   |   |
| Age                                                   | Questionnaire                                                                       | X |   |   |   |   |
| Gender                                                | Questionnaire                                                                       | X |   |   |   |   |
| Education level                                       | Questionnaire                                                                       | X |   |   |   |   |
| Work situation                                        | Questionnaire                                                                       | X |   |   |   |   |
| Duration of complaints                                | Questionnaire                                                                       | X |   |   |   |   |
| Possible co-morbidities                               | Questionnaire                                                                       | X |   |   |   |   |

